### Confounders

In all multivariate analyses, we will adjust for key characteristics of the index event, including the PEPP category, the length of the index event, diagnoses of index event (dementia, substance abuse, schizophrenia and schizoaffective disorder, bipolar disorder and manic episodes, major depressive disorder, post-traumatic stress disorder, and personality disorder), the necessity for intensive treatment (OPS-Code 9–61), whether the admission was an emergency admission, other prescribed or certified DM measures (medication, remedies and aids, home care, outpatient intensive care specialized outpatient palliative care, patient transportation, digital health applications, and incapacity certificate). We will also control for participants' medical history prior to the index hospitalization, as such previous psychiatric hospitalizations, comorbidities in form of the Elixhauser Comorbidity Index [14] and care level. As for demographic variables, we will include age, sex, population density at the place of residence and the German Index of Socioeconomic Deprivation [15] (Table 2).

**Table 2 Tab2:** Variables

Category	Variable	Operationalization
Exposure	Sociotherapy	Prescription of Sociotherapy as a DM measure (ITT) / Prescription of Sociotherapy as a DM and utilization of at least one sociotherapy session (PPA)
Index event	PEPP	PO/PP/PA/TP/QA
	Length of index event	Number of days of index event
	Dementia	F00.x– F03.x, G30.x
	Substance abuse	F10.2, F11.2, F12.2, F13.2, F14.2, F15.2, F16.2, F17.2, F18.2, F19.2
	Schizophrenia & Schizoaffective disorder	F20.x, F21.x; F25.x
	Bipolar disorder & Manic episodes	F30.1– F30.2, F31.1– F31.2, F31.4- F31.6
	Major depressive disorder	F32.2– F32.3; F33.2– F33.3
	Post-traumatic stress disorder	F43.1
	Personality disorder	F60.x– F61.x
	Intensive treatment	OPS 9–61
	Emergency admission	Reason for admission
Discharge management measures (presciptions and certificates)	Medication	
	Remedies and aids	
	Home care	
	Outpatient intensive care	
	Specialized outpatient palliative care	
	Patient transportation	
	Digital health applications	
	Incapacity certificate	
Medical history	Elixhauser Comorbidity Index [16]	Based on all available diagnoses twelve months prior to the index event
	Number of psychiatric hospital days	Hospital stays with PEPP categories PO, PP, PA, TP & QA based on all available data twelve months prior to the index event
	Care level	Based on care level on the last day prior to the index event
Sociodemographic	Age	
	Sex	
	Population density at place of residence	NUTS 3 (Destatis data)
	German Index of Socioeconomic Deprivation (GISD) at place of residence	NUTS 3 (GISD data)

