The main focus of the present paper is sociotherapy, an intervention that aims to support individuals with severe mental health disorders (i.e., schizophrenia, bipolar disorder or chronic depression). This patient-centered approach was included as a key measure in the 2017 German health care reform to improve DM and is especially relevant for psychiatric patients. As a form of structured case management, sociotherapy aims to improve coordination among healthcare providers involved in a patient’s treatment and support patients in utilizing needed healthcare services. Further goals are to foster social participation through the engagement of the patient’s social network and to offer crisis intervention if needed. In line with the Recovery Framework in mental health, the focus of sociotherapy does not lie on reducing psychiatric symptoms but rather emphasizes practical, social and daily life skills [3, 4]. Among other measures, sociotherapy ultimately aims to reduce or shorten psychiatric hospital stays [5]. Sociotherapy is typically provided by trained mental health professionals, including social workers, psychiatric nurses, and specialized therapists. Sociotherapy can be prescribed as a transitional DM measure, ideally starting immediately after discharge. To this end, an initial prescription can be issued by the hospital that lasts up to seven days, after which continued treatment requires a prescription from a licensed outpatient health care professional. In total, up to 120 sociotherapy sessions can be prescribed over a three-year period [6].

Sociotherapy as implemented in Germany shares similarities with various forms of case management found in other countries, particularly in the context of mental health care. For example, models such as Case Management (CS), Intensive Case Management, Critical Time Intervention (CTI), or Care Programme Approach (CPA) in the United Kingdom also emphasize coordinated, patient-centered care aimed at supporting individuals with severe mental illnesses [7]. Commonalities include involvement of the patient’s social network, and a focus on improving access to necessary health and social services. However, there are notable differences: the German sociotherapy framework is embedded in statutory health insurance, whereas similar programs elsewhere might operate under different funding mechanisms, timeframes or case load.

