### Assignment procedures

To address potential confounding in the observational data we estimate propensity scores based on the probability of receiving sociotherapy. These scores will be calculated using logistic regression controlling for key characteristics of the index event, other prescribed DM measures, medical history and sociodemographic characteristics (for a detailed description see Table 2). Afterwards the propensity scores will be applied by either propensity score matching (PSM) or inverse probability weighting (IPW) depending on the distribution of the scores. Balance diagnostics such as standardized mean differences will be conducted and all steps of the procedure including the applied methods will be reported.

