### Follow-up period

We follow up with participants for 30 days after discharge to assess the primary outcome, and for up to 365 days for secondary outcomes, or until death—whichever occurs first. During the follow-up period, we will evaluate the continuation of sociotherapy prescriptions as a component of a structured DM, as well as any new prescriptions issued in the outpatient setting.

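### The adjustment set in Table 2 has no pre-index outpatient psychiatric care or psychotropic treatment, which could leave residual confounding of unknown direction

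*Protocol article*

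**What the plan says.** The protocol article uses one set of variables twice. Under Assignment procedures the propensity score is built by "controlling for key characteristics of the index event, other prescribed DM measures, medical history and sociodemographic characteristics (for a detailed description see Table 2"). Under Confounders the same groups of variables enter every adjusted model, with medical history given as "as such previous psychiatric hospitalizations, comorbidities in form of the Elixhauser Comorbidity Index [14] and care level".

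Table 2 gives medical history three entries:
- the Elixhauser index, "Based on all available diagnoses twelve months prior to the index event";
- psychiatric hospital days, defined as "Hospital stays with PEPP categories PO, PP, PA, TP & QA based on all available data twelve months prior to the index event";
- care level.

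Drugs appear only among the "other prescribed or certified DM measures (medication, remedies and aids, home care" and so on, that is, as something the hospital prescribes at the end of the index event. No drug class is given.

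Outpatient information is used elsewhere in the plan, always about sociotherapy itself. Outpatient prescriptions in the prior 365 days lead to exclusion (Eligibility criteria). Follow-up records continuation "as well as any new prescriptions issued in the outpatient setting". The per-protocol definition depends on sessions used.

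The Discussion names social determinants (social support, family, employment) as confounders that cannot be accounted for. It mentions outpatient service use only as an outcome that is not studied.

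**The concern.** Confounding by indication is the main threat to a causal reading of this comparison. By the article's own account (Background), sociotherapy is meant to "support patients in utilizing needed healthcare services" and to coordinate the providers involved. After the first week, "continued treatment requires a prescription from a licensed outpatient health care professional".

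A patient who already sees a psychiatrist or psychotherapist, or who is already on psychotropic treatment, therefore differs from one who does not in ways that plausibly bear on two things: whether the hospital prescribes sociotherapy, and whether the patient is soon readmitted. Both characteristics precede the prescription, so adjusting for them is not adjusting for a mediator.

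The direction cannot be read from the documents. Hospitals might prescribe more often to patients without outpatient care, because the need is greater, or to patients with it, because someone can continue the prescription. Existing care might lower readmission through continuity, or mark a more severe illness. Whatever imbalance the listed variables do not capture would pass into the estimated effect of sociotherapy.

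**Working it through.** **Step 1: does any listed variable measure the missing items?**
- Psychiatric hospital days cover inpatient, semi-inpatient and inpatient-equivalent stays only.
- The Elixhauser index uses diagnoses. It counts neither contacts nor dispensing, and the article does not say whether outpatient diagnoses are included.
- The medication item is a discharge-management prescription. The Background limits such measures to seven days after discharge, so it does not describe earlier treatment.
- Index diagnoses, emergency admission, intensive treatment and care level describe severity and need, not prior outpatient care.

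These are partial proxies. None measures outpatient psychiatric contact or earlier psychotropic use.

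**Step 2: is there a look-back period?** Claims cover 2021 to 2024 and index events fall in 2022 to 2023. At least twelve months precede every index event, and Table 2 already uses that window.

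**Step 3: possible size.** The plan has no figure on this point to reproduce, so every input here is an assumption. For one binary omitted variable with prevalence pT (treated) and pC (control) remaining after adjustment, and risk ratio RR for readmission, the treatment risk ratio is multiplied by

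(1 + pT(RR − 1)) / (1 + pC(RR − 1)).

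| pC | pT | RR = 0.7 | RR = 1.5 |
|---|---|---|---|
| 0.40 | 0.60 | 0.82/0.88 = 0.93 | 1.30/1.20 = 1.08 |
| 0.50 | 0.70 | 0.79/0.85 = 0.93 | 1.35/1.25 = 1.08 |
| 0.60 | 0.80 | 0.76/0.82 = 0.93 | 1.40/1.30 = 1.08 |
| 0.60 | 0.40 | 0.88/0.82 = 1.07 | 1.20/1.30 = 0.92 |
| 0.45 | 0.70 | 0.79/0.865 = 0.91 | 1.35/1.225 = 1.10 |

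The range is 0.91 to 1.10. Other assumptions give other answers. With RR from 1.5 to 2.5 and gaps of 10 to 30 points, the factor runs from 1.25/1.20 = 1.04 (0.50 against 0.40, RR 1.5) to 2.05/1.60 = 1.28 (0.70 against 0.40, RR 2.5). The primary model estimates an odds ratio, so these risk-ratio factors are approximate for it.

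**Step 4: comparison with the target effect.** The sample size section gives an effect size of 0.3 without its metric. Read as a downward shift of 0.3 on the normal (probit) scale, it is a risk ratio of about 0.57 at a 10% baseline and 0.63 at 20%. The factor would move these to between 0.57 × 0.91 = 0.52 and 0.63 × 1.10 = 0.69. Read instead as Cohen's h, the target is about 0.29 (10%) to 0.48 (20%).

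**Step 5: room for more parameters.** Table 2 implies about 29 covariate terms: PEPP category 4, length of stay 1, diagnoses 7, intensive treatment 1, emergency admission 1, discharge measures 8, medical history 3 (care level as one term), sociodemographics 4. If the stated N of 449 is a total, a 10% readmission rate gives 449 × 0.10 ≈ 45 events, and fewer if sociotherapy works. The outcome model is therefore already sparse at that size. The propensity model is limited by the number of prescriptions, not by readmissions.

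**The case against.** The case on the other side has real weight.

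- **Data access is not shown.** A reader might infer that outpatient contacts and dispensing are already in hand because outpatient records are used elsewhere. The documents do not support that. The outpatient items shown concern sociotherapy, the source is described only as claims data, and contact and dispensing fields are not itemised. This stands, so the remedy has to be conditional.
- **No indication rule based on service use is stated.** The Background describes the target group by diagnosis, and Table 2 adjusts for schizophrenia, bipolar disorder and severe depression. The outpatient prescriber is needed for continuation, not for the hospital's first prescription, which is the exposure. This stands too: the link is an inference from the aims of sociotherapy.
- **The proxies remove part of the bias.** Prior hospital days, index diagnoses, emergency admission, care level and the exclusion of recent sociotherapy users all help. Only the remainder matters, and its size is unknown.
- **The list may be open-ended, or a fuller plan may extend it.** The Confounders text can be read as giving examples. But Table 2 is presented as the detailed description and goes down to diagnosis codes, so the article fixes the set and does not leave it to another document. This part does not stand.
- **More covariates cost precision.** This stands for the outcome models, given step 5, but much less for the propensity score.

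**Conclusion.** The gap is real. Followed as written, the plan balances and adjusts for hospital-based psychiatric history but not for pre-index outpatient psychiatric or psychotherapeutic care or psychotropic treatment. This could leave residual confounding of unknown sign.

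A reader might go further and conclude that the primary effect is certainly biased, or that the target effect could be explained away. The documents support neither. On the assumed inputs in the main table, the distortion is about 9% downward to 10% upward on the risk-ratio scale. That would not abolish an effect of the planned size, but it could produce an apparent effect of that order when there is none, or blur a smaller true one. The size depends on the assumed residual imbalance and risk ratio, and the comparison with the target depends on an effect-size metric that the article does not state.

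No false statement is involved. The weakness is an adjustment set narrower than the article's own account of the intervention suggests, together with a Discussion that does not disclose it. It is worth correcting before the analysis, but it does not invalidate the design.

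**What to change.** Add a compact set to the propensity score, measured in the existing 12-month look-back:
- number of quarters with an outpatient psychiatrist or psychotherapist contact;
- any psychotropic dispensing, by broad class.

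Both depend on the fields being in the extract. If they are not, use the number of quarters with an outpatient psychiatric (F) diagnosis, provided the extracted diagnoses include outpatient ones.

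Report the standardized mean differences of these variables before and after matching or weighting, against the existing 0.1 criterion under Descriptives. Carry them into the outcome models only as far as the number of events allows.

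If none of these variables can be obtained, name the gap in the Discussion beside the social determinants.

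The cost is a few derived covariates, a few more model parameters, and possibly a supplementary request for data fields.

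### The bipolar and major depression flags in Table 2 cover only some subcodes of the disorders they are named for, so confounding by indication may remain among unflagged patients

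*Protocol article*

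**What the plan says.** The Confounders section of the protocol article lists the index diagnoses to be adjusted for in all multivariable models. Besides dementia, substance abuse and schizophrenia, these are "bipolar disorder and manic episodes, major depressive disorder, post-traumatic stress disorder, and personality disorder". No severity limit is attached to any of these names.

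Table 2 then fixes the codes:

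- Bipolar disorder and manic episodes: "F30.1– F30.2, F31.1– F31.2, F31.4- F31.6".
- Major depressive disorder: "F32.2– F32.3; F33.2– F33.3".
- Substance abuse: "F10.2, F11.2, F12.2, F13.2, F14.2, F15.2, F16.2, F17.2, F18.2, F19.2".
- Schizophrenia and schizoaffective disorder: "F20.x, F21.x; F25.x".
- Dementia: "F00.x– F03.x, G30.x".

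The last two rows take every subcode (.x), as does the personality disorder row. The first three rows do not, and the article gives no reason for the difference.

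The same variables feed the propensity model. The Assignment procedures section says "These scores will be calculated using logistic regression controlling for key characteristics of the index event". The Background describes the target group of sociotherapy as "individuals with severe mental health disorders (i.e., schizophrenia, bipolar disorder or chronic depression".

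**The concern.** By the document's own account, bipolar disorder and chronic depression are reasons to prescribe sociotherapy, and bipolar and major depressive disorder are confounders to be adjusted for. A patient whose index stay is coded F31.3, F31.9 or F33.1 nevertheless gets 0 on the relevant flag. If no other flag applies, that patient joins the reference group of patients with none of the named disorders. Within that group, some patients have a condition for which sociotherapy is meant and others do not, and the diagnosis variables cannot tell them apart.

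If the two kinds of patient differ both in the chance of a prescription and in the risk of readmission, the comparison is confounded there. Adjusting twice, in the propensity score and again in the outcome model, does not help, because both use the same flags. Standardized mean differences calculated on the flags can be below 0.1 while the hidden subgroup is unbalanced. The Discussion names only social determinants as unmeasured confounders, so a reader of the results would not be alerted.

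**Working it through.** **Step 1: labels against codes.** Subcodes not captured, by flag:

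| Flag | Not captured |
|---|---|
| Bipolar and manic episodes | F30.0, F30.8–F30.9, F31.0, F31.3, F31.7–F31.9 |
| Major depressive disorder | every F32 and F33 subcode except .2 and .3 |
| Substance abuse | every F10–F19 subcode except .2 |

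The gap at F31.3 and the contrast with the .x rows are visible in Table 2 itself. That the other subcodes exist, and what they denote, comes from the structure of ICD-10. Three of the seven diagnosis flags are affected. The dementia, schizophrenia, post-traumatic stress and personality disorder flags cover the categories they name.

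**Step 2: which gaps concern the indication.** The Background names bipolar disorder and chronic depression but not substance use. Confounding by indication can therefore be argued for the first two flags only. For the third, the label is wider than the codes, which leaves an ordinary confounder partly adjusted.

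**Step 3: possible size.** The article gives no figure on this point, so there is none to reproduce. All inputs below are assumptions. There is no true treatment effect, and the results apply only among patients with no flag.

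*Illustration A.* Let s be the share of omitted-code patients among the unflagged, and k their relative chance of prescription. With prescription rare, their share is about s among controls, and among the treated it is s·k / (s·k + 1 − s). Take k = 5.

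- s = 5%, readmission risk 20% against 10%: treated share 0.25/1.20 = 20.8%. Risks are 10% + 0.208 × 10% = 12.1% and 10% + 0.05 × 10% = 10.5%. OR = (0.1208/0.8792)/(0.105/0.895) = 1.17.
- s = 10%, same risks: treated share 0.50/1.40 = 35.7%. Risks are 13.6% and 11.0%. OR = 1.27.
- s = 10%, risk 15% against 10%: risks are 11.8% and 10.5%. OR = 1.14.

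*Illustration B.* Assume a 1% prescription probability and a 10% readmission risk in unaffected patients. Let ORx and ORy be the odds ratios of omitted-code patients for prescription and for readmission. The share s is as before, and the shares in each arm are computed exactly.

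| s | ORx | ORy | Share treated / control | Risk treated / control | Spurious OR |
|---|---|---|---|---|---|
| 5% | 2 | 1.5 | 9.4% / 5.0% | 10.40% / 10.21% | 1.02 |
| 15% | 2 | 2 | 25.9% / 14.9% | 12.12% / 11.22% | 1.09 |
| 15% | 4 | 2 | 40.7% / 14.6% | 13.33% / 11.20% | 1.22 |
| 30% | 4 | 2 | 62.5% / 29.4% | 15.11% / 12.40% | 1.26 |

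First row in full: the odds of prescription are 2 × 0.01/0.99, a probability of 1.98%. The odds of readmission are 1.5 × 0.1/0.9, a risk of 14.29%. The treated share is 0.05 × 0.0198 / (0.05 × 0.0198 + 0.95 × 0.01) = 9.4%. The treated risk is 10% + 0.094 × 4.29% = 10.40%.

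At a 20% baseline the same rows again lie between 1.02 and 1.26. The OR is exactly 1 if either ORx or ORy is 1.

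**Step 4: dilution.** The estimand is the average effect among the treated, so the bias is weighted by the share w of treated patients who are unflagged. Assume the same control risk elsewhere and no bias there. The overall treated risk is then w × (unflagged treated risk) + (1 − w) × (control risk). For the first two cases of Illustration A:

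- w = 20%: 10.82% against 10.5% and 11.51% against 11.0%, ORs 1.03 and 1.05.
- w = 50%: 11.29% against 10.5% and 12.29% against 11.0%, ORs 1.08 and 1.13.

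The true w is unknown.

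**The case against.** The strongest defence is that the lists are a severity cut. Read with ICD-10, the codes kept are mainly manic, mixed and severe depressive states. Those left out include hypomania, mild or moderate bipolar depression, remission and non-severe unipolar depression. Skipping F31.3 parallels keeping only .2 and .3 of F32 and F33, and the Background does speak of severe disorders. If prescribing follows severity, omitted-code patients may resemble the reference group more than a fivefold chance of prescription implies.

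Much of this stands. A severity cut is a plausible reading of most of the gaps, and nothing in the article supports the assumed shares, prescription ratios or risks. But the article neither states such a cut nor labels the variables as severe. It does not account for F31.8 or F31.9, since an unspecified code is not evidence of mildness. The Background's list also names bipolar disorder as such. Even an intended cut leaves patients with and without the disorder mixed at flag = 0.

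A second defence is that other covariates carry the information. Psychiatric hospital days in the prior year, PEPP category, length of stay, emergency admission and the Elixhauser index may absorb part of the bias, and a patient missed by one flag may carry another. This also stands. A reader might infer that the planned models are blind to the difference, and that goes too far. The cover is only partial, however: the Elixhauser index uses diagnoses from the twelve months before the index event, not the index diagnosis.

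**Conclusion.** The mismatch between named confounders and coded flags is on the page, and it applies to bipolar disorder, major depression and substance abuse. For the first two it leaves room for confounding by indication that balance checks on these flags would not reveal. For substance abuse it is incomplete adjustment for an ordinary confounder.

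The size is unknown. Under the assumed inputs, the spurious OR among unflagged patients is about 1.02 to 1.27, from negligible to moderate. The overall effect is smaller, in proportion to the share of treated patients without a flag.

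A reader might infer that the plan will make sociotherapy look worse. The documents do not establish that. It follows only if omitted-code patients are both prescribed sociotherapy more often and readmitted more often, in which case a benefit would be masked. If one of those associations is absent there is no bias, and if one is reversed the bias changes sign. The masking case still deserves attention, because the Conclusion says a null result could lead to reconsidering insurance coverage. The change is worth making before analysis.

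**What to change.** In Table 2, replace each of the three two-level flags by a three-level variable:

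- no diagnosis of the disorder;
- the disorder with a code now listed;
- the disorder with any other subcode of F30–F31, F32–F33 or F10–F19 respectively.

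A patient with codes of both kinds goes to the level with the listed codes. Use these variables in the propensity score, the balance table (with a standardized mean difference for each level) and the outcome models. If a severity cut is intended, say so in the Confounders section; the second level then preserves it.

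The cost is an edit to the code list. Index diagnoses must be extracted for the present flags anyway, so no new data source is needed. Each variable gains one term, three in all. Some of the new levels may be sparse, so a rule for collapsing them should be fixed before outcomes are examined.

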### Design

The aim of this study protocol is to describe the emulation of a target trial designed to estimate the causal effect of sociotherapy as a DM measure using observational data from insurance claims records. Following the principles of TTE, we define the hypothetical RCT that we seek to emulate [8, 9]. Based on the primary outcome of interest (30-day readmissions), the sample size for the target trial was calculated. We then provide a detailed description of the TTE using observational data, covering key aspects such as included variables, eligibility criteria, treatment strategies, assignment procedure, follow-up period and outcomes definitions (for a comparison between hypothetical target trial and emulation see Table 1). And finally, we outline the statistical analysis strategy for the TTE.

**Table 1 Tab1:** Target Trial Emulation

	**TARGET TRIAL**	**E2-PSY TRIAL EMULATION**
Eligibily Critera	Inclusion criteria • Adults aged 18 years or over • Patients with a psychiatric treatment in an inpatient, semi-inpatient or inpatient equivalent setting Exclusion criteria • Previous sociotherapy	Inclusion criteria • • Adults aged 18 years or over • Patients with a psychiatric treatment in an inpatient, semi-inpatient or inpatient equivalent setting (PEPP classification PO, PP, PA, TP, or QA) Exclusion criteria • Previous sociotherapy within 365 days before the last day of the index event • No continuous health insurance throughout the study period • Personnal of the insurance provider supplying the data • Existing data protection notice • Existing objection to use of healthcare records for research purposes
Treatment Strategies	Intervention group • Prescription of sociotherapy as acomponents of discharge management (last day of the index event) Control group • No prescription of sociotherapy as a componentof discharge management (last day of the index event)	Intervention group • Prescription of sociotherapy as a components of discharge management (last day of the index event) Control group • No prescription of sociotherapy as a component of discharge management (last day of the index event)
Assignment procedures	Participants will be randomly assigned to either treatment armon the last day of the index event. Patients will be aware of the treatment armthey have been assigned to	Quasi-randomization will be archived through a propensity score-based method, either propensity score matching or inverse probability weighting

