Follow-Up Period	Starts at randomization and ends 30 days/365 days after discharge of the index event, death, or loss to follow-up	Starts at the last day of the index event and ends 30 days/365 days after discharge of the index event, death, or loss to follow-up
Outcome	Primary outcome • Readmission to hospital for psychiatric treatment within 30 days after discharge Secondary outcomes • Readmission to hospital for psychiatric treatment within 365 days after discharge • Time to first psychiatric rehospitalization • Total number of rehospitalizations within 365 days after discharge • Cumulative number of days spent in the hospital due to psychiatric admissions during 365 days after discharge	Primary outcome • Readmission to hospital for psychiatric treatment within 30 days after discharge Secondary outcomes • Readmission to hospital for psychiatric treatment within 365 days after discharge • Time to first psychiatric rehospitalization • Total number of rehospitalizations within 365 days after discharge • Cumulative number of days spent in the hospital due to psychiatric admissions during 365 days after discharge
Causal Contrasts Of Interest	• Intention-To-Treat (ITT): The ITT evaluates the average treatment effect among the treated (ATT), regardless of whether the patients adhered to the treatment • Per-Protocol (PPA): The PPA evaluates the average treatment effect among the treated (ATT), accounting for the non-adherence to the sociotherapy treatment in the intervention group, and usage of sociotherapy in the control group due to prescriptions of sociotherapy unrelated to the assignment procedure	• Intention-To-Treat (ITT): The ITT evaluates the average treatment effect among the treated (ATT), regardless of whether the patients adhered to the treatment • Per-Protocol (PPA): The PPA evaluates the average treatment effect among the treated (ATT), accounting for the non-adherence to the sociotherapy treatment in the intervention group, and usage of sociotherapy in the control group due to prescriptions of sociotherapy unrelated to the assignment procedure

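### Table 2 closes the Elixhauser look-back and care level before admission although time zero is the last day of the index event, leaving a small, avoidable gap in confounder adjustment

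*Protocol article*

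**What the plan says.** **Time zero.** Table 1 (Design) gives the emulation's follow-up as "Starts at the last day of the index event and ends 30 days/365 days after discharge of the index event". Treatment strategy is fixed on the same day: the target-trial column describes the control arm as "No prescription of sociotherapy as a componentof discharge management (last day of the index event", and the emulation column uses the same anchor.

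**Medical history.** Table 2 (Confounders) defines the three variables in this block as follows:
- Care level: "Based on care level on the last day prior to the index event".
- Elixhauser Comorbidity Index: "Based on all available diagnoses twelve months prior to the index event".
- Psychiatric hospital days: "based on all available data twelve months prior to the index event".

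The running text agrees: "We will also control for participants' medical history prior to the index hospitalization".

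**Information from the stay.** The same section states that "we will adjust for key characteristics of the index event, including the PEPP category, the length of the index event, diagnoses of index event". It adds "the necessity for intensive treatment", emergency admission and the other discharge-management measures. Under Assignment procedures, the propensity score draws on the same groups of variables.

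**The concern.** In a target trial emulation, whatever is known before assignment can serve as baseline information. Here the index event is a period whose length is itself a covariate, and assignment falls at its end. A comorbidity index and a care level that stop at admission therefore leave an interval, as long as the stay, in which new information precedes the prescription but enters neither variable. Under Outcomes, same-day transfers between settings continue the index event, so the interval can span several settings.

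A condition first documented in hospital, or a care level changed there, may bear on whether sociotherapy is prescribed and on whether the patient returns. If both links exist, some confounding remains that the data could have removed. The Discussion already concedes that social support, family and employment status cannot be controlled for, which is a reason not to add an avoidable gap. The same covariates feed the propensity score and all multivariate models, so no later step repairs it.

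**Working it through.** The plan states no figure on this point, so the check is mainly a comparison of each covariate's time window with time zero.

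**Step 1: windows in Table 2**

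| Block | Variables | Window |
|---|---|---|
| Index event | 11: PEPP category, length, seven diagnosis groups, intensive treatment, emergency admission | The index event |
| Discharge management | 8 prescriptions or certificates | Discharge |
| Medical history | 3: Elixhauser index, prior psychiatric hospital days, care level | Ends before the index event |
| Sociodemographic | 4: age, sex, population density, deprivation index | Not at issue |

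That makes 11 + 8 + 3 + 4 = 26 covariates. Three stop before admission. For prior psychiatric hospital days this is appropriate, because the days of the index stay are already carried by its length. Two of the 26 are left.

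**Step 2: what the in-stay flags pick up.** The seven groups are dementia (including G30.x), substance dependence (F10.2 to F19.2), schizophrenia and schizoaffective disorder, bipolar disorder and mania, major depression (F32.2–F32.3, F33.2–F33.3), post-traumatic stress disorder and personality disorder. A diagnosis first coded in the stay reaches the models as a diagnosis only if it falls in one of these.

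**Step 3: what drops out.** Somatic conditions first coded in the stay (G30.x apart), substance codes other than F1x.2, and any change of care level between admission and the last day. For the diagnoses, the loss is limited to codes that the Elixhauser definition counts.

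**Step 4: anchors within the plan.** The exclusion for previous sociotherapy looks back 365 days from the last day of the index event, so it covers the stay. The comorbidity look-back does not. No reason is given for the difference.

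**Step 5: illustration of size. All inputs are assumptions; none comes from the documents.** Take one binary comorbidity with prevalence 0.35 in the treated and 0.25 in controls, and a readmission risk ratio of 1.6 (an excess of 0.6).

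- No adjustment: (1 + 0.35 × 0.6) / (1 + 0.25 × 0.6) = 1.21 / 1.15 = 1.052.
- Adjustment for a recorded version with sensitivity *s* and specificity 1, standardised to the treated:
  residual factor = 1.21 / {0.35*s* × 1.6 + (1 − 0.35*s*) × [1 + 0.6 × 0.25(1 − *s*)/(1 − 0.25*s*)]}.
- At *s* = 0.8: 0.28 × 1.6 = 0.448; 0.72 × (1 + 0.6 × 0.05/0.80) = 0.747; 1.21 / 1.195 = 1.013.
- At *s* = 0.6: 0.21 × 1.6 = 0.336; 0.79 × (1 + 0.6 × 0.10/0.85) = 0.846; 1.21 / 1.182 = 1.024.

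| Share captured by the pre-admission window | Residual factor | Share of log bias left |
|---|---|---|
| 90% | 1.006 | 13% |
| 80% | 1.013 | 25% |
| 70% | 1.018 | 36% |
| 60% | 1.024 | 46% |

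The illustration treats the comorbidity as the only confounder and ignores every other covariate in the model. Care level is not quantified.

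**The case against.** The strongest reply is that the plan is coherent as it stands. Text and table agree on the cut-off, and the plan separates history (before admission) from features of the index event (during it). A pre-admission look-back for a comorbidity index is a common and defensible convention. That stands: this is not an error or an inconsistency.

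Second, a reader might infer that in-stay baseline information is left out in general, or that a substance disorder first recorded in the stay is in no model. The documents do not support either reading. Eleven index-event variables and eight discharge measures are adjusted for, and dependence codes F10.2 to F19.2 are among the flags. Home care, outpatient intensive care, remedies and aids, and palliative care plausibly also mark somatic burden and care need. Length of stay is adjusted for too, which weakens any argument from long stays or merged transfers.

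Third, it is not shown that late-coded information drives the prescription. The Background says that discharge planning must begin as early as possible, and the documents do not say how often comorbidities are newly coded or care levels changed during a stay. The outcome is psychiatric readmission, whereas most of what is lost is somatic. This limits the likely size of the problem but does not remove the gap.

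Fourth, extending the window has some cost. In-stay codes could be counted both in the index and in the flags, complications of the stay would be mixed with existing illness, and longer stays give more opportunity to code. These are fair points. The overlap can be avoided, and length of stay is already in the models.

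**Conclusion.** The point holds in a narrow form. Two covariates, the Elixhauser index and care level, close before admission while assignment and follow-up start on the last day of the index event. Comorbidity first coded in the stay outside the seven flagged groups, and care-level changes during the stay, therefore enter neither the propensity score nor the outcome models as such.

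The consequence is a small, avoidable source of residual confounding whose size cannot be determined from the documents. The factors of 1.006 to 1.024 show only what one moderately imbalanced comorbidity could leave under the assumed prevalences, risk ratio and capture; they are not an estimate for this study. It would be wrong to conclude that the plan contradicts itself or that the primary result is seriously threatened. This is a worthwhile low-cost improvement, because the plan already treats other in-stay information as baseline and gives no reason for handling these two variables differently.

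**What to change.** Change two cells of Table 2, and the matching phrase on medical history in the Confounders text:

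- **Elixhauser index:** diagnoses from the 12 months before admission plus the index event's own diagnoses up to its last day. To avoid double counting, leave codes already covered by the seven flags out of the in-stay part.
- **Care level:** the value on the last day of the index event.
- **Prior psychiatric hospital days:** no change.

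If the authors prefer the pre-admission cut-off, one sentence giving the reason would suffice.

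The cost is small. Index-event diagnoses must be extracted for the flags anyway, and everything added precedes time zero. Some complications of the stay will enter the index, and longer stays will contribute more codes, but length of stay is already adjusted for. The sample-size figures (N = 449 and N = 329) do not depend on this point.
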